#### Placebo

This is commercially available 0.9% saline solution in vials.

Patients will receive 5 ml of the study drug containing 5 mg, 60 mg, or 125 mg solnatide or 0.9% saline according to treatment allocation via endotracheal nebulization every 12 h for a maximum of 7 days using an Aeroneb Solo nebulizer.

Reconstituted solnatide as well as placebo solution (saline) will be supplied in a closed and labelled syringe to study personnel authorized for administration. Both solutions are clear and colorless, and thus indistinguishable in appearance.

#### Dosing and administration

In this dose ascending study, 3 groups of patients (one for each dosage) will be randomized to treatment with either solnatide or placebo. The three doses administered in this study are 5 mg, 60 mg, and 125 mg and escalation from one dose to the next will occur only once a DSMB has carefully reviewed the safety data emerging from the last treatment group and has approved the administration of the next highest dosage. The highest dosage used in this study has already been tested and has proved to be safe in a Phase I and two Phase II trials and no dose-limiting effects are expected.

Patients will be treated with solnatide or placebo twice a day for 7 days via endotracheal inhalation. Inhalations should be scheduled around 08:00 a.m. (± 30 min) and 08:00 p.m. (± 30 min). The 12-h sequence should be followed as closely as possible. If applicable to the routine of the ICU, inhalation can be shifted to a later time until 10:00 a.m. (± 30 min) and 10:00 p.m. (± 30 min), respectively, at the latest.

To enable endotracheal inhalation, reconstituted solnatide in water for injection is converted into an inhalable aerosol by the Aeroneb Solo medicinal device. This device is a product of Aerogen, Galway, Ireland, and is a commercially available liquid nebulizer. The Aerogen Solo nebulizer has been approved in the European Community by CE-marking based on requirements of Annex II, Section 3.2. of Directive 93/42/EEC.

The nebulizer unit holds up to 6 ml of liquid medication. The nebulizer unit is clear to allow visual monitoring of medication levels and aerosolization. When the nebulizer unit is connected to the ventilator circuit, the silicon plug can be opened and closed in between doses without causing loss of circuit pressure.

The T-piece of the nebulizer connects the unit into the breathing circuit via standard male and female 22-mm conical ports. The nebulizer unit together with the T-piece is placed into the inspiratory limb of the breathing circuit before the patient wye. Various in vitro studies and laboratory simulation have been conducted to characterize solnatide aerosol generation by the Aeroneb Solo nebulizer. Solnatide solution of 25 mg/ml showed effective nebulization and small condensation losses of solnatide aerosol in the connecting tube system. The nebulization time for 5 ml ranges between 10 and 20 min. Breath simulator studies showed that approx. 60 to 70% of nebulized solnatide was deposited on the inhalation filter (“lung”), indicating that the delivered dose of solnatide corresponds to about 60 to 70% of the nominal nebulizer filling dose.

### Criteria for discontinuing or modifying allocated interventions {11b}

Discontinuation from treatment does not mean discontinuation from the study, and remaining study procedures should be completed as indicated by the study protocol as described for any treatment day as well as follow-up period. If a clinically significant finding is identified (including, but not limited to changes from baseline) after enrolment, the investigator or qualified designee will determine if any change in participant management is needed. Any new clinically relevant finding will be reported as an adverse event (AE).

Every subject, the legal representative or authorized representative has the right to interrupt or to discontinue study participation at any time, for any reason, and every subject may be discontinued from the study for any reason beneficial to his/her wellbeing.

In addition, individual subjects must discontinue or withdraw from the study for any of the following reasons:
Withdrawal of informed consent by the patient or the legal representative or authorized representative.Any AE, laboratory abnormality or intercurrent illness that, in the opinion of the investigator, indicates that continued participation in the study is not in the best interest of the subject.Suspected drug-related serious adverse event (SAE)Suspected unexpected serious adverse reaction (SUSAR)Allergies or idiosyncrasies to solnatide.

Patients withdrawn from the study will not be replaced with new participants.

If the cause of temporary withdrawal has been resolved, e.g., informed consent has been re-confirmed, a suspected drug-related SAE has not been confirmed by the investigator, a SUSAR has not been confirmed by the investigator, the patient may resume participation in the clinical study if the treatment schedule allows it.

Patients who are withdrawn from the study prematurely by the investigator or the sponsor will undergo all investigations as described for any treatment day for the end-of-study interview. Patients, the legal representative, or authorized representative who withdraw consent will be asked to accept further safety examinations in the interest of the patient.

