#### Exclusion criteria

Patients must meet none of the exclusion criteria listed below.
History of clinically relevant allergies or idiosyncrasies to solnatide.Known use of any other investigational or non-registered drug within 30 days or within 5 half-lives of these drugs prior to study enrolment, whichever is longer. No exceptions are allowed in this study.Severe state of septic shock with a mean arterial pressure (MAP) ≤ 65 mmHg and a serum lactate level > 4 mmol/L (36 mg/dl) despite adequate volume resuscitation.An underlying clinical condition that, in the opinion of the investigator, would make it very unlikely for the patient to be successfully weaned from ventilation due to severe underlying diseases (e.g., severe malnutrition, severe neurological diseases, pulmonary fibrosis, or COPD).Extracorporeal membrane oxygenation, high-frequency oscillatory ventilation or any form of extracorporeal lung support. In no way are patients to be denied or delayed these procedures to avoid exclusion from the study.Neutrophil count < 0.3 × 10^9^/L.Cancer treatment (chemotherapy or biological) or therapy with other immunosuppressive agents for organ transplantation within 2 weeks.Cachexia (BMI < 18.5 kg/m^2^).Unequivocal cases of cardiogenic pulmonary edema (if differential diagnosis based on an ARDS triggering condition and clinical replicability is not possible, echocardiography may be indicated).Severe skin burns involving more than 15% of body surface.Subjects who are extremely unlikely to survive more than 48 h due to the acute conditions of the patient in the opinion of the investigator.Subjects transferred from a hospital not participating in this study who are already planned to be re- transferred during the observation period.Subjects who are not expected to survive the next month because of an underlying uncorrectable medical condition or a do not resuscitate order.Women known to be pregnant, women who are lactating, women with a positive or indeterminate pregnancy test, on screening, and males of reproductive potential and women of childbearing potential who are not willing to use highly effective methods of birth control/contraception for a duration defined in the patient’s Informed Consent Form.After randomization, drop-out of a participant is not envisaged by the protocol except for withdrawal of consent by the participant or his/her legal representative, discontinuation of the treatment (e.g., due to toxicity, or death of the patient during the treatment course).

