### Procedure for unblinding if needed {17b}

Individual patient unblinding during the trial may occur in case of patient emergencies or medically important adverse events including cases of COVID-19.

The code breaking procedure is managed by means of an online-specific utility implemented in the eCRF and is available for the investigator and pharmacovigilance staff only. Sealed envelopes will also be provided as backup in the unlikely case of system unavailability.

If during the study the investigator needs to break a code (for emergency reasons), he/she has to follow the procedure implemented in the system clicking on ad hoc icon present on the toolbar.

In case of an individual patient unblinding, an automatic email will be sent to the study team notifying the occurrence of a code break reminding the investigator to discontinue the patient from the study.

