The same analysis will be repeated for SAEs regardless of drug relationship, for drug-related SAEs, AEs with an outcome of death, and AEs leading to discontinuation of treatment. Deaths reportable as SAEs will be listed by patient and tabulated by MedDRA SOC and PT.

#### All-cause deaths through day 28

The number and proportion of deceased patients will be reported. In addition, the time (in days) from randomization to the event will be used for analysis. Subjects without an event will be censored at the earlier of the last contact date or day 28. The Kaplan-Meier estimates of the survival functions for each treatment cohort will be plotted and summarized.

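### Study-withdrawal rules triggered by suspected drug harm or unblinding contradict the rule that stopping treatment is not leaving the study, and can end scheduled safety follow-up before day 28

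*Protocol article*

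**What the plan says.** Item 11b (criteria for discontinuing or modifying interventions) opens with a clear principle: "Discontinuation from treatment does not mean discontinuation from the study". Remaining procedures are to be completed.

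The same item then states that "individual subjects must discontinue or withdraw from the study for any of the following reasons". Besides withdrawn consent, the list names AEs, laboratory abnormalities or intercurrent illness that the investigator judges to make continued participation against the subject's interest, then "Suspected drug-related serious adverse event (SAE)Suspected unexpected serious adverse reaction (SUSAR"), and allergy or idiosyncrasy to solnatide. It goes on: "Patients who are withdrawn from the study prematurely by the investigator or the sponsor will undergo all investigations as described for any treatment day", for an end-of-study interview. A temporarily withdrawn patient may return if the cause has been resolved, for example because the suspicion was not confirmed, and if the treatment schedule permits.

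Two other places bear on the same patients:
- Item 17b (unblinding): "Individual patient unblinding during the trial may occur in case of patient emergencies or medically important adverse events including cases of COVID-19". The code break sends an automatic e-mail "reminding the investigator to discontinue the patient from the study".
- The closing sentence of the exclusion criteria gives, among the exceptions to a general rule of no drop-out, "discontinuation of the treatment (e.g., due to toxicity, or death of the patient during the treatment course").

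On analysis, the section on all-cause deaths through day 28 says: "Subjects without an event will be censored at the earlier of the last contact date or day 28". The safety analysis section applies no missing-data method. The section on serious adverse event reporting requires every SAE up to at least 28 days after randomization to be reported, and makes no exception for withdrawn patients.

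**The concern.** Safety is the main objective (Objectives) and the registered primary outcome (administrative table). The DSMB decides on each dose escalation from safety data of the 28-day study period (Trial design).

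If the withdrawal list is followed as worded, patients in whom drug harm is suspected leave scheduled observation early, while other patients are observed to day 28. A toxic dose would produce more such exits than placebo. Censoring that depends on suspected toxicity is not independent of the risk of death or of further harm, so estimates for the affected arm can be too favourable. The same holds for code breaks made because of a medically important AE.

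A statistical analysis plan cannot repair this later, because data that were never collected cannot be recovered.

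**Working it through.** **Step 1: the texts side by side.**

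| Place | What ends | What follows |
|---|---|---|
| 11b, opening | Treatment | Remaining study procedures continue |
| 11b, list | Study participation (compulsory) | End-of-study investigations; conditional return |
| 17b | Study participation, after any code break | Nothing further stated |
| Exclusion criteria, last sentence | Treatment, classed as drop-out | Nothing further stated |
| SAE reporting | – | All SAEs reported to at least day 28 |

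The first row cannot stand with the next three for a patient whose treatment stops because of suspected toxicity. The last row keeps SAE reporting open but schedules no assessments.

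**Step 2: what is at risk.** The planned analyses cover all AEs to day 28, laboratory values and vital signs to day 14, and ECG over the first 7 days. For a patient permanently withdrawn under these rules, no collection of these after the end-of-study investigations is stated. Vital status at day 28 would be known only if a death were reported as an SAE.

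**Step 3: possible size for mortality (illustration).** The plan gives no figure on this point to reproduce.

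Inputs:
- Arm size 20 (Sample size).
- Mortality *m* = 40.3% in patients not withdrawn. This is the hospital mortality for moderate ARDS in the Introduction; applying it to 28 days is an assumption.
- Mortality *q* = 60%, 80% or 100% in withdrawn patients: assumed.
- Number withdrawn *w* = 2 or 4, before any death, censored at withdrawal, with no later death captured: assumed.

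True arm mortality = [(20 − *w*)·*m* + *w*·*q*] / 20. Kaplan-Meier, with the withdrawn censored, estimates *m*. The shortfall is therefore (*w*/20)·(*q* − *m*).

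| *w* | *q* | True mortality | Kaplan-Meier | Shortfall (points) |
|---|---|---|---|---|
| 2 | 60% | (18 × 0.403 + 2 × 0.60)/20 = 42.3% | 40.3% | 2 |
| 2 | 80% | (18 × 0.403 + 2 × 0.80)/20 = 44.3% | 40.3% | 4 |
| 2 | 100% | (18 × 0.403 + 2 × 1.00)/20 = 46.3% | 40.3% | 6 |
| 4 | 60% | (16 × 0.403 + 4 × 0.60)/20 = 44.2% | 40.3% | 4 |
| 4 | 80% | (16 × 0.403 + 4 × 0.80)/20 = 48.2% | 40.3% | 8 |
| 4 | 100% | (16 × 0.403 + 4 × 1.00)/20 = 52.2% | 40.3% | 12 |

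If *q* = *m* the shortfall is zero. It also vanishes if the deaths after withdrawal are captured through SAE reporting.

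**Step 4: worst case, labelled as such.** The plan also reports the crude proportion of deceased patients. If no death after withdrawal were captured and the denominator stayed at 20, the crude figure would be 18 × 0.403/20 = 36.3% (*w* = 2) or 16 × 0.403/20 = 32.2% (*w* = 4). That is 6–10 or 12–20 points below the true values above. The SAE reporting rule speaks against this case.

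**The case against.** The strongest reply is that the loss is much smaller than the withdrawal wording suggests.

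- **Deaths and SAEs.** A reader might infer that deaths and late SAEs after the trigger go uncounted. The documents do not support that. SAE reporting runs to at least day 28 without exception for withdrawn patients, the safety analyses treat deaths as reportable SAEs, and only subjects without an event are censored. The Discussion also assumes that patients stay in the study hospital throughout. This stands, and it narrows the point to scheduled data and confirmed vital status.
- **Return.** A reader might infer that every suspicion means permanent loss. Item 11b allows return when the suspicion is not confirmed. This stands too, but it leaves permanent loss concentrated in confirmed cases.
- **Intent.** Because return depends on the treatment schedule, the list may have been meant for dosing only. That is possible, but the text says study, as does item 17b.
- **Timing.** Item 11b does not say when the end-of-study investigations take place, and the schedule figure is not shown. An immediate final visit is therefore not established.
- **Analysis sets.** A reader might infer that removing unblinded or COVID-19 patients breaks the ITT set. Nothing removes them from it. Lost follow-up is missing data, not exclusion, and safety is analysed on the Safety Set.
- **Frequency and consequence.** The article reports no drug-related SAEs or SUSARs in previous studies, so two or four withdrawals in 20 is an assumption. The triggering events themselves are reported and tabulated, and no numerical mortality threshold for escalation is given.

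The contradiction remains after all of this, as does the absence of stated scheduled follow-up for these patients.

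**Conclusion.** The point holds as a contradiction with a possible informative-censoring consequence, not as proof that harm will be missed. Followed as written, items 11b and 17b end scheduled safety follow-up for patients selected by suspected harm or unblinding, in a trial whose main objective is safety and whose escalation rests on 28-day safety data. The likely direction is towards making a dose look safer.

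The size cannot be read from the documents. Under the stated assumptions, the Kaplan-Meier shortfall is about 2–6 points with 2 of 20 withdrawn and 4–12 points with 4 of 20. One patient is 5 points of a 20-patient arm, so these gaps amount to roughly half a patient to two and a half patients. They need higher mortality in the withdrawn and deaths that SAE reporting does not catch; without either condition the shortfall is zero. The loss of non-serious AEs, laboratory values, vital signs and ECG does not depend on those mortality assumptions.

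**What to change.** Reconcile item 11b, item 17b, the last sentence of the exclusion criteria, the SAE reporting section and the text of the code-break e-mail. State that these triggers, whatever they mean for study treatment (left to the sponsor), do not end safety and vital-status follow-up.

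Collect AEs and SAEs, the safety assessments already scheduled, and day-28 vital status for every randomized patient unless consent to follow-up is withdrawn. Report 28-day all-cause mortality on that basis. Survival to day 28 needs recording as well as death: if only deaths are captured while survivors are censored early, Kaplan-Meier can err in the other direction.

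The cost is a wording change in a few places, one automatic e-mail, and a few more follow-up contacts. The study period already runs to day 28.

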### Strategies to improve adherence to interventions {11c}

The study medication will be administered only by authorized study personnel. Every effort will be made to ensure timely administration of the IMP as per protocol. If medication cannot be administered, the reason is to be documented in the eCRF and a protocol deviation recorded.

### Relevant concomitant care permitted or prohibited during the trial {11d}

There are no known interactions of solnatide with other substances. Accordingly, a general list of permitted and not-permitted concomitant medication is not available. In previous clinical studies, no drug- related SAEs and SUSARs have been observed.

As this is an add-on study in patients also receiving standard treatment, administration of concomitant medication is subject to the investigator’s decision and discretion and may vary for each individual patient due to the heterogeneity of ARDS and underlying etiologies.

### Provisions for post-trial care {30}

Specific post-trial care is not provided. Study participants are insured against any harm arising from the study interventions according to legal provisions.

### Outcomes {12}

The main objective of this study is to investigate the safety of solnatide administration. Therefore, no formal primary and secondary outcomes are defined. Safety will be assessed by a review of mortality, incidence of adverse events, and serious adverse events, as well as by analysis of relevant laboratory data and ECG. The following parameters will be taken into account when assessing the safety of solnatide:
Vital signs (i.e., heart rate, systolic and diastolic blood pressure, and temperature)Clinical laboratory (i.e., white and red blood cell count, hematocrit, hemoglobin concentration, platelet count, creatinine, sodium, potassium, chloride, blood urea nitrogen, bilirubin, aspartate and alanine transaminases, lactate dehydrogenase, amylase, lipase, C-reactive protein, creatine kinase, arterial pH, PaO_2_, PaCO_2_, bicarbonate, SO_2_ as well as urine pH, specific weight, appearance, color, nitrites, proteins, glucose, urobilinogen, bilirubin, ketones, hematic pigments, and leukocytes)12-lead electrocardiogramHemodynamic parameters (i.e., mean arterial pressure, pulmonary blood volume, cardiac index, and cardiac outputNeed for vasoactive drugs24-h fluid balanceConcomitant medicationsAll-cause deathsUtilization of extracorporeal treatmentsAdverse events and serious adverse events

The secondary objective of this study is to evaluate possible endpoints for a future Phase III pivotal trial. Such endpoints investigated in this study include:
Extravascular lung water indexPulmonary vascular permeability indexMurray lung injury scoreOxygenation ratioVentilation parameters (i.e., plateau pressure, tidal volume, positive end-expiratory pressure, peak inspiratory pressure, respiratory rate, F_i_O_2_, mean airway pressure, peak airway pressure, ventilation mode)Lung complianceVentilation-free daysDays of ICUDays of hospitalizationDriving pressureSequential organ failure assessment

### Participant timeline {13}

The intended timeline for each participant’s study activities is outlined in Fig. 2.

**Fig. 2 Fig2:**
[figure not shown]
Schedule of activities

### Sample size {14}

Given that the primary objective of the study is to investigate the safety of solnatide, the study sample size of 95 randomized patients is based on feasibility criteria.

Patients will be randomized to 3 groups of 20 patients each, representing the 3 multiple ascending dose groups receiving solnatide at doses of 5 mg, 60 mg and 125 mg, and 35 patients will receiving placebo in total, with 15 patients receiving placebo in Dosing Group A (low dose) and Dosing Group B (middle dose) and 20 patients receiving placebo in Dosing Group C (high dose).

Nevertheless, considering the key preliminary efficacy endpoint and the results of a Phase IIa study (2012-001863-64), a sample size of 20 evaluable patients in each treatment group will have approximately 80% power to detect a difference in means between solnatide and placebo of 3.2 ml/kg in the change from baseline to day 7 of EVLWI with a common SD of 3.5 using a two-group *t*-test with a 0.05 two-sided significance level and no alpha level adjustment for multiple testing.

### Recruitment {15}

All ARDS patients in participating centers will be screened for eligibility. In case of slow or insufficient recruitment, the sponsor will consider increasing the number of study sites.

## Assignment of interventions: allocation

### Sequence generation {16a}, concealment mechanism {16b} and implementation {16c}

A randomization plan will be generated before study start. No stratification factors are planned. Three different randomization lists (one for each step of the study) will be prepared with the following randomization ratios:
2:1 in the first step of solnatide 5 mg vs. placebo4:1 in the second step of solnatide 60 mg vs. placebo4:1 in the third step of solnatide 125 mg vs. placebo

The randomization process will be managed electronically (block-wise generation of random numbers) by means of an Interactive Web Response System (IWRS) to ensure that treatment assignment is unbiased and concealed from patients and investigator staff. The results of the randomization are merely revealed to the responsible study pharmacist, who will then facilitate the preparation of the respective IMP. IMP vials are transferred to the investigators in a neutral container. Solnatide and placebo solutions cannot be distinguished from one another by the investigators.

